### EEG data analysis

EEG data will be preprocessed using a hierarchically organized pipeline proceeding as follows [59]. Data will be first segmented into contiguous epochs after a preliminary investigation on which epoch length is the most robust for analyses. Then, a 2nd-order infinite Butterworth forward and backward filter with a 0.5–45 Hz low-pass high-pass filter at a resolution of 2 Hz (500 ms time windows) with a Hanning taper window will be applied. Eye movements or muscle-related artifacts will be removed using a common Independent Component Analysis (ICA), supervised and manually corrected after expert visual verification. Epochs with signals exceeding 120μv peak-to-peak amplitude will be also removed. Finally, channels will be re-referenced to their common average. Once data pre-processing is completed, (i) power spectrum density (PSD), (ii) connectivity, and (iii) complexity measures will be calculated. These approaches will be individually conducted on each subject for every condition or task (resting-state recordings, visuo-motor adaptation task, AX-CPT task, associated to everytime point of our study timeline (baseline, post-tDCS, follow-up).

 A time-frequency analysis will be conducted in order to explore pre tDCS (baseline) vs. post  tDCS and vs. follow-up tDCS-related modulations of patients’ oscillatory activity. To this end, the amplitude of the power spectrum density ($$\mu {V}^{2}$$) for each frequency band (δ: 0.5–4 Hz; θ: 4–8 Hz; α: 8–12 Hz; β: 12–30 Hz; γ: 30–60 Hz) will be computed by means of a Fast Fourier Transformation (FFT) using Welch’s method with a 500-ms periodogram. Relative and absolute spectral normalized power (NP) will be then extracted for each EEG electrode. Normalized average power for all frequency bands will be computed and plotted to explore differences between pre-tDCS (baseline) vs. post-tDCS and vs. follow-up milestones within each group and to compare differencesacross independent groups stimulated with different tDCS approaches.

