## Statistical analyses

In order to evaluate the therapeutic potential of each tDCS intervention in post-stroke motor recovery, we will first asses the data distribution of the Fugl-Meyer Assessment by means of Shapiro–Wilk method. In the case of normal distribution, clinical outcomes will be compared using repeated measures analysis of variance (two-way ANOVA) with “TIME” (baseline, post-tDCS, follow-up) as within-subject factor, and “GROUP” (ipsi-DLPFC, contra-CEREB, ipsi-DLPFC + contra-CEREB, SHAM) as between-subject factor. Post hoc pair-wise comparisons will be performed using a Bonferroni correction for multiple comparisons. In the case of non-normal data distribution, a non-parametric Kruskal–Wallis test will replace repeated measures ANOVA. Linear mixed models and Pearson’s (for normally distributed data) or Spearman's correlation coefficients corrected for multiple comparisons between AX-CPT, visuo-motor adaptation task, and the Fugl-Meyer outcomes will be used to explore behavioral correlation between motor, attentional, and cognitive control domains. All data will be presented as mean ± standard deviation and statistical significance will be set for all tests at *p* ≤ 0.05.

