In order to characterize the electrophysiological EEG effects induced by our interventions, we will first explore correlations with behavioral data and biomarkers of recovery. First, power spectral density (PSD) changes for each frequency band will be compared between stimulation groups using two-tailed ANOVA (*P* = 0.05), with “TIME” as the within-subject factor and “GROUP” as the between-subject factor. To correct for multiple comparisons, non-parametric cluster-based permutation statistics with Montecarlo sampling (1000 permutations) will be applied, allowing the examination of global effects across all electrodes while controlling for multiple comparisons at the sensor level, without the need of prior assumptions about effect location. Finally, connectivity (imaginary part of coherence measures) and entropy effects (complexity of temporal dynamics) of the electrophysiological response will be also explored. The same statistical procedure as for PSD exploration applying repeated measures ANOVA with non-parametric cluster-based permutation statistics and MonteCarlo sampling (1000 permutation) will be used, with “TIME” as within factor, and “GROUP” as between factor. Individually averaged connectivity and entropy values (total averages) and individual topographical maps at the electrode level will be examined to detect specific regions sensible to the tDCS intervention.

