The individual differences across the study follow-up for the Fugl-Meyer Assessment evaluating upper/lower limb motor recovery,visuo-motor adaptation task outcomes assessing cerebellar contributions to motor learning and the AX-CPT task assessing sustained attention and cognitive control will be correlated (Pearson’s or Spearman correlation coefficients, depending on data normality) with the individuals’ electric fields voxel-by-voxel magnitude (an underneath cut-off of 0.25 V/m in total field strength will be positioned as a threshold in the power to induce neuronal effects). Moreover, the |E| and |nE| extracted values and the total injected current will be also correlated with the same outcome measures. Otherwise, E-field components will be correlated with specific EEG features reaching statistical significance in the power spectrum density ($$\mu {V}^{2}$$), connectivity, and complexity analyses. Finally, multivariate regression models will be computed to explore correlations between electrophysiological responses ($$\mu {V}^{2}$$, imaginary coherence and entropy measures), induced E-field, and behavioral outcomes.

All data will be analyzed according to the intention-to-treat principle. The data of all patients with complete datasets (at W0, W3, and W7 time points ) will be analyzed according to their randomized tDCS group. All available data will be included in the analysis. Missing data will be imputed by means of a constrained longitudinal data analysis (cLDA) which will estimate unconditionally lost data.

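### With 1000 permutations fixed for the EEG cluster tests, verdicts close to 0.05 can depend on the random seed; raising the number is a cheap, minor improvement

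*Protocol article*

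**What the plan says.** The section Statistical analyses sets the number of permutations twice. For spectral power by frequency band, "non-parametric cluster-based permutation statistics with Montecarlo sampling (1000 permutations) will be applied". For connectivity (imaginary coherence) and entropy, "non-parametric cluster-based permutation statistics and MonteCarlo sampling (1000 permutation) will be used".

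The threshold is fixed in the same section: "statistical significance will be set for all tests at *p* ≤ 0.05". For the power comparisons it is restated: they "will be compared between stimulation groups using two-tailed ANOVA (*P* = 0.05").

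The section EEG data analysis shows how often the procedure may be used. It lists five bands ("δ: 0.5–4 Hz; θ: 4–8 Hz; α: 8–12 Hz; β: 12–30 Hz; γ: 30–60 Hz"), three kinds of measure ("i) power spectrum density (PSD), (ii) connectivity, and (iii) complexity measures will be calculated") and three kinds of recording ("resting-state recordings, visuo-motor adaptation task, AX-CPT task, associated to everytime point of our study timeline"). It does not state a number of tests.

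The verdicts are used again later in Statistical analyses: "E-field components will be correlated with specific EEG features reaching statistical significance in the power spectrum density", and likewise for connectivity and complexity.

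**The concern.** A permutation p-value from a random sample of permutations is an estimate with binomial error. When the exact p is far from 0.05 that error is harmless. When it is near 0.05, two analysts with the same data, the same code and different seeds can reach opposite verdicts.

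Two features of the plan give this some weight. The procedure is applied to many band, measure and recording combinations, so some exact p-values may fall near the threshold. And significance acts as a filter for the E-field correlations, so a verdict that turns on the seed would also decide which of those correlations are run. The noise is avoidable: with 8 channels and 60 patients, more draws cost little.

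**Working it through.** The article states no Monte Carlo error and no repeat-run disagreement rate, so there is no figure of its own to reproduce.

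**Inputs.** From Statistical analyses: B = 1000 permutations, threshold 0.05. From EEG data analysis: 5 bands, 3 measures, 3 recordings. Assumed: the number of tests K, their independence, and no true effect (exact p uniform on 0 to 1).

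**Step 1: error of one p-value.** SE = √(p(1−p)/B).
- B = 1000: √(0.05 × 0.95 / 1000) = 0.0069. The 95% range is 0.05 ± 1.96 × 0.00689, that is 0.0365 to 0.0635.
- B = 10,000: √(0.05 × 0.95 / 10,000) = 0.0022. The 95% range is 0.0457 to 0.0543.

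**Step 2: disagreement for one test.** Let q(p) = P(Bin(B, p) ≤ 0.05B), the chance that a run declares significance when the exact p-value is p. Two independent runs disagree with probability 2q(1−q). For B = 1000:

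| Exact p | Two runs disagree |
|---|---|
| 0.03 | under 0.1% |
| 0.035 | 1.1% |
| 0.04 | 9% |
| 0.045 | 32% |
| 0.05 | 50% |
| 0.055 | 39% |
| 0.06 | 18% |
| 0.065 | 5% |
| 0.08 | under 0.1% |

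Averaged over uniform p, the rate is f = 0.00782 per test with B = 1000 and f = 0.00246 with B = 10,000. The ratio is 0.00782 / 0.00246 = 3.2.

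**Step 3: at least one disagreement in K tests.** 1 − (1 − f)^K.

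| Assumed K | How obtained | B = 1000 | B = 10,000 |
|---|---|---|---|
| 7 | 5 bands + connectivity + entropy, one recording | 5.4% | 1.7% |
| 15 | 5 bands × 3 recordings | 11.1% | 3.6% |
| 21 | 7 × 3 recordings | 15.2% | 5.0% |
| 63 | 21 × 3 ANOVA effects | 39.0% | 14.4% |

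**Step 4: sensitivity, B = 1000, K = 15 and 21.**
- Tests equally correlated at 0.8: 9.3% and 11.9%.
- A true effect in every test (z-shift 1 to 2.8): about 23-33% and 30-43%.
- p computed as (b+1)/(B+1), where b is the number of permuted statistics at least as extreme as the observed one: 11.0% and 15.1%.
- One run compared with the exact verdict, instead of two runs with each other: 0.556% per test, giving 8.0% and 11.0%.

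**Step 5: level of the test.** With B = 1000 the type I error is 0.04995 using (b+1)/(B+1) and 0.051 using b/B.

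**The case against.** The strongest reply is that nothing is wrong: 1000 draws is a conventional number, the test holds its level (step 5), and asking for more is a preference about computing precision. The first two parts stand. A reader might infer from the seed dependence that the EEG tests are invalid or inflate false positives; step 5 shows that they do not. What remains is reproducibility of individual verdicts, which a correct average error rate does not secure.

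Three other stronger readings are also unsupported:
- A reader might infer that every EEG p-value carries this noise. The correlations with behavioural data, the E-field correlations and the regression models in Statistical analyses, and the correlations with resting-state EEG in Biophysical E-field models, are not described as permutation-based.
- A reader might take 11-15% as a property of the plan. It depends on a test count inferred from the text, on independence and on no true effects. The plan also foresees no second run, although the comparison with the exact verdict (step 4) gives rates of similar size.
- A reader might argue that 1000 draws are too coarse for a Bonferroni threshold such as 0.05/15. The article sets no such threshold for these tests; it uses 0.05, with the cluster procedure as the sensor-level correction.

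It is also fair to say that borderline results need not occur. Under uniform p, an exact p falls between 0.0365 and 0.0635 with probability 0.027, so at least one does so in 1 − 0.973^15 = 34% to 1 − 0.973^21 = 44% of analyses. The significance filter is partial too: the regressions and the correlations in Biophysical E-field models are not described as depending on it. Finally, the random seed and the exact p-value formula are commonly left to an analysis plan, so their absence from the article is no finding.

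**Conclusion.** The point holds as a minor precision issue, not as an error or contradiction. The stated 1000 permutations leave EEG verdicts with an exact p of roughly 0.035 to 0.065 open to the choice of seed, and those verdicts select features for the E-field correlations.

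The size is uncertain because the article gives no test count: about 5% to 39% for at least one disagreement between two runs over the range of 7 to 63 tests, with 11-15% for the middle reading of 15-21, all under independence and no true effects.

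Materiality is low. The Outcome measures section makes EEG a secondary outcome, the Sample size section calls the study exploratory, and the primary analysis of FMA-UE uses no permutation test.

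**What to change.** In Statistical analyses, replace 1000 with at least 10,000 permutations in both places: the sentence on power and the sentence on connectivity and entropy. This reduces the disagreement rate about threefold but does not remove it; with 100,000 draws it would be 1.2-1.6% for 15-21 tests.

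When the analysis code is written, it is sensible to record the seed and compute p as (b+1)/(B+1). A recorded seed makes a result repeatable but does not make a borderline verdict less arbitrary, so it does not replace the larger number.

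The cost is some computing time. Data collection, sample size and clinical procedures do not change.

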### Exit criteria

Patients will be dropped out from the study if: (1) they manifest, at any time and without the need to provide any explanation, their willingness to stop their participation in the clinical trial; (2) they are not compliant with the procedures of the study; (2) they experience severe discomfort or annoyance during their participation (i.e., insomnia, headache, etc.); or (3) in case of unexpected events that incapacitate patients to continue in the study. Data collected until a participant is officially considered a 'drop-out' will be included in analyses, hence not withdrawn from the study.

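### The plan gives incompatible instructions on which patients enter the FMA-UE analysis, and treats cLDA as an imputation step for an ANOVA instead of as the analysis

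*Protocol article*

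**What the plan says.** The last paragraph of Statistical analyses makes four statements in succession:

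- On the principle: "All data will be analyzed according to the intention-to-treat principle".
- On whose results are compared by randomised group: "The data of all patients with complete datasets", with completeness defined over the three assessment visits.
- On the same question, one sentence later: "All available data will be included in the analysis".
- On gaps in the record: "Missing data will be imputed by means of a constrained longitudinal data analysis (cLDA) which will estimate unconditionally lost data".

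The first paragraph of the same section names the test for the clinical outcomes: repeated-measures ANOVA (TIME by GROUP) if FMA is normally distributed, Kruskal-Wallis if not. Linear mixed models appear there only for relations between the behavioural domains.

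Exit criteria lists reasons for leaving the study that include "they are not compliant with the procedures of the study" and "they experience severe discomfort or annoyance during their participation". It adds: "Data collected until a participant is officially considered a 'drop-out' will be included in analyses, hence not withdrawn from the study".

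**The concern.** An analyst who follows the complete-datasets sentence has nothing to impute. One who follows the all-available-data sentence must set the complete-datasets sentence aside. The named test does not settle the matter, because a standard repeated-measures ANOVA needs every visit from every patient. It leads either to completers only or to a filled-in data set.

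cLDA is neither. It models all observed visits jointly, with one baseline mean common to the arms, and estimates the group differences directly from incomplete data. It does not itself produce a completed data set, and the article does not say how its output would reach the ANOVA.

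At stake is the primary comparison. A completer analysis gives up the protection of randomisation if leaving is related to tolerance or recovery. Predictions analysed as if observed understate the standard error. With 15 patients per arm, 10–20% missing is only 1.5 to 3 patients per arm, yet the result could depend on which sentence is followed.

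**Working it through.** **Inputs from the article.** 4 arms × 15 = 60 patients, which agrees with the stated total; FMA-UE at W0, W3 and W7; significance at 0.05; a 6-point within-patient improvement described as clinically significant. The article gives no SD, between-visit correlation, drop-out rate or power calculation, so there is no planned figure to reproduce.

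**Textual check.**

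| Instruction | Patients analysed | Anything to impute? |
|---|---|---|
| Intention-to-treat | all randomised | yes |
| Complete W0/W3/W7 datasets | completers | no |
| All available data | all with data | not under a likelihood model |
| Imputation by cLDA | all | yes |
| Repeated-measures ANOVA | completers, or a filled-in set | depends on the set |

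**Simulation A (assumed: SD 15, correlation 0.9, W7 missing).** There were 1000 trials per scenario with 4 arms of 15. The contrast was W7 change, combined arm minus sham, with no Bonferroni step.

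Hand check of the scale: SD of change = 15 × √(2 × (1 − 0.9)) = 6.71. With nobody missing, SE of the difference = 6.71 × √(2/15) = 2.45. With 12 completers per arm it is 6.71 × √(2/12) = 2.74, against 2.73 in the simulation.

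Completely random drop-out, true difference 0, one cLDA fill-in and then a t-test:

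| Missing | Reported SE | Actual SD of estimate | Ratio | Type I error |
|---|---|---|---|---|
| 10% | 2.32 | 2.44 | 0.95 | 5.1% |
| 20% | 2.23 | 2.67 | 0.84 | 9.9% |
| 30% | 2.12 | 2.80 | 0.76 | 12.5% |

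The reported SE falls below the 2.45 that would apply with no missing data at all, which is the false precision. The completer estimate stayed unbiased here (−0.08 to 0.02).

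Drop-out depending on the observed W3 change, in opposite directions in sham and active arms (a deliberately adverse case; base rates 10/20/30%):

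| True difference | Completers only | cLDA fitted directly |
|---|---|---|
| 0 | 1.25 / 1.89 / 2.57 | −0.07 / −0.02 / 0.07 |
| 6 | 6.91 / 7.53 / 8.02 | 5.99 / 6.09 / 6.11 |

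In this case, with true difference 0, fill-in followed by the t-test had type I error of 8.2%, 11.3% and 17.9%.

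**Simulation B (4000 trials; missing follow-up predicted from baseline; completely random missingness).** With arm-specific prediction, type I error was about 7–8%, 10–11% and 12–13% at 10%, 15% and 20% missing. With prediction pooled over arms it was about 5%. Taking A and B together for arm-specific prediction gives roughly 5–13% at 10–20% missing.

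**Loss that depends on the outcome itself (assumed SD of change 6).** If the worst 20% of one arm leave, the mean of the rest shifts by SD × φ(z₀.₂)/0.8 = 6 × 0.280/0.8 = 2.10 points, and 2.10/6 = 0.35 of the 6-point threshold. If those patients leave before W3, only their baseline is known, and a baseline-adjusted likelihood analysis still leaves about 1.6–2.0 points of bias (correlation 0.5–0.9).

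**The case against.** The strongest reply is that this is loose wording. The complete-datasets sentence never says only. The next sentence, the intention-to-treat statement and Exit criteria all point to everyone randomised. A reader might infer that the plan restricts the analysis to completers; the text does not support that, since it is one of two readings. That stands, but the conflict remains, and because the article itself states it, an unseen analysis plan could resolve it only by contradicting one of these sentences.

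A reader might also infer that every reading biases the result. It does not: completers are unbiased if drop-out is completely random, and proper multiple imputation would avoid the false precision. The article states neither.

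The error rates test a single fill-in that the article does not spell out, and pooled prediction shows no inflation. This also stands, so they are given as a range and as a consequence of one possible reading.

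Nothing in the article shows that drop-out would be more frequent under active current. The sham is built to mimic the ramp sensations, and Safety monitoring expects no major side effects. Differential drop-out is a possibility raised by the listed exit reasons, no more. Nor does Exit criteria say outright that W3 and W7 are not collected after exit; it says only that data up to that point are kept.

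The trial is a pilot without a power calculation. It nevertheless tests at 0.05, so the analysis set still matters.

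**Conclusion.** The concern holds as a contradiction in the text. Intention-to-treat, complete datasets, all available data, imputation by cLDA and a repeated-measures ANOVA cannot be followed together, and cLDA is misdescribed.

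The sizes are illustrative. A single arm-specific fill-in raises pairwise type I error from 5% to roughly 5–13% with 10–20% missing at random. In the adverse case tried, completers show a spurious difference of 1.25–2.57 points when the truth is zero. Both rest on assumed SD, correlation, drop-out rate and mechanism. cLDA fitted directly showed no material bias when drop-out was random or depended on observed scores.

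It would be wrong to infer that cLDA also removes the 2.1-point shift from losing the worst 20% of one arm. That is a not-at-random case, and only continued outcome collection addresses it.

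**What to change.** 1. Name cLDA as the primary analysis in place of the repeated-measures ANOVA, fitted directly to all available FMA-UE at W0, W3 and W7 from all randomised patients.
2. Remove the description of cLDA as imputation.
3. Delete the complete-datasets sentence, or label it a sensitivity analysis.
4. Reconcile Exit criteria with intention-to-treat: state that the W3 and W7 FMA-UE already scheduled are still collected from patients who end stimulation, where they consent and are able. This leaves unchanged who stops stimulation, and must be worded consistently with Safety monitoring, under which participation ceases after a major adverse event.

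The cost is a change of analysis wording and a short amendment on follow-up. The method is already named in the article and the visits are already scheduled, so the added burden is small. The change should be made before unblinding.

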## Discussion

The current study protocol (*E-Brain*) aims at assessing the immediate and longer-term clinical potential of ten accumulative sessions of anodal high-density tDCS in patients with upper limb motor disability during the chronic phase  of a unilateral middle cerebral artery stroke. The novelty of our protocol is that instead of aiming to directly modulate damaged motor areas or their contralesional homologues, it focuses on assessing the isolated or combined stimulation of two regions such as the ipsilesional prefrontal cortex (DLPFC) and the contralateral anterior cerebellar lobe (CEREB), not directly involved (as premotor and primary motor systems do) in the execution of motor activity, but instead contributing indirectly to such via the modulation of associated cognitive processes.

A high number of prior conventional NIBS stimulation studies using repetitive TMS or tDCS in post-stroke motor dysfunctions have based their interventions on (i) the upregulation (with anodal tDCS, high-frequency rTMS or iTBS patterns) of ipsilesional M1/premotor systems; (ii) the downregulation (with cathodal tDCS, low-frequency rTMS, or cTBS patterns) of spared contralesional M1/premotor systems by virtue of the trans-callosal rivalrous mutually inhibitory  interactions, remapping, reorganizing, or normalizing abnormal excitability levels in lesional and perilesional areas [62]; or (iii) the upregulation of motor control/coordination systems such as the supplementary motor area (SMA) or the cerebellum. Unfortunately, initial enthusiasm for many of these approaches tested in small clinical trials has dwindled due to the lack of consistent effects when evaluated in larger populations of patients, and efficacy remains debated [63]. For this reason, it is paramount to explore and provide proof-of-concept for new treatments based on the manipulation of cortical sites, with the ability to drive improvements by acting on spared 'non-purely motor ' regions indirectly contributing to the recovery of voluntary motion via the modulation of associated cognitive processes and network-synchronization mechanisms.

In the cognitive domain, anodal tDCS over the ipsilesional DLPFC and/or cathodal stimulation of the contralesional DLPFC have shown efficacy in the modulation of prefrontal functions such as sustained attention and cognitive control [64–66]. Likewise, the modulation of the anterior lobe of the cerebellum has shown promise in stroke patients, given its active role in motor learning, and motor coordination, and its ability to contribute to motor “reorganization” when premotor or primary corticospinal systems are severely damaged [32–34]. Additionally, the neural signature of middle cerebral artery damage has revealed interactions between alterations of sustained attention deficits and impairments of motor function, emphasizing the importance of inter-areal communication in motor rehabilitation [20], hence the need for restorative stimulation methodologies able to integrate large-scale network-wide synchronization mechanisms across these structures. However, limitations in terms of spatial resolution posed by clinical EEG with few recording sensors-useful to explore the clinical evolution of neurophysiological markers in individual patients-has limited our comprehension of the underlying processes subtending motor recovery in stroke. Moreover, technical limitations of the first generation of tDCS devices to implement multi-site stimulation (i.e., targeting with acceptable spatial resolution via high-density montages different cortical nodes simultaneously) have contributed to keeping 'network' neuromodulation approaches poorly explored.

In such context, the protocol *E-Brain* aims at comparing in separate and independent patient groups three active anodal tDCS conditions (ipsi-DLPFC, contra-CEREB, ipsi-DLPFC + contra-CEREB) and a SHAM tDCS intervention. Our design will contribute to identifying the most beneficial strategy comparing single-site (monofocal) or combined (bifocal) dual-site approaches by means of high-density tDCS. The study will also ascertain changes in DLPFC and anterior cerebellar lobe modulation by means of tasks specifically assessing sustained attention/cognitive control and visuo-motor adaptation skills respectively, to verify that upper limb motor improvements are mediated by the modulation of such contributing networks. Moreover, different EEG synchrony measures recorded along the intervention will report on local and “large-scale” modulations of primary motor systems from distant regions, via changes in functional connectivity and local and long-range synchronization mechanisms [67] and reveal the longer-term neuroplastic properties associated with such effects.

Still a key challenge for clinical neuroscience [68, 69], this approach is currently inspiring a transition from conventional “single-site” neuromodulation focused on targeting directly impaired systems, towards multifocal stimulation set-ups with multiple electrical sources able to address more holistically, network dysfunction [70, 71]. Moreover, it is supported for example by recent work demonstrating higher modulatory power on cortical reactivity [66] and changes in corticospinal excitability [72, 73] by dual-site (bifocal) stimulation as compared to single-site (monofocal) tDCS approaches. In this context, our protocol will be among the first fully adopting the notion of post-stroke motor paralysis as a network impairment involving not only motor but also non-motor cognitive systems contributing indirectly to voluntary motion. Under such perspective, we will pursue the modulation of network dysfunction via a circuit-based therapeutic approach and promote local and global synergistic network-wide effects (“reshaping”) between non-purely primary motor regions (such as the prefrontal cortex and the anterior cerebellar lobe) and motor and premotor systems to facilitate motor post-stroke rehabilitation and effective recovery.

Our protocol is however not exempt from risk and might suffer from potential limitations, which we will try to minimize. First, recovery of lost motor function occurs slowly and gradually. Thus, the ten sessions of stimulation and a monthly follow-up planned for our patients might not be sufficient to drive or account for significant motor skill re-acquisition. Nonetheless, a more intense (i.e., a higher number of daily and cumulated sessions over time) and longer-lasting regime or follow-up period is currently outside of the scope of our protocol and limited by the scarcity of available time and resources. Two weeks of stimulation and a single monthly post-treatment follow-up seems a reasonable compromise for an experimental trial that once proven potentially successful, can be developed at a larger scale. Second, stroke patients even if sharing the same cardinal symptom, upper hand motor paralysis, can be differently affected by types of lesional mechanisms, lesion volume and lesion location, impacting the severity of the impairments, their ability to fully understand and perform motor or cognitive tasks hence compromise the reliability of behavioral and EEG evidence. Therefore, even if the *MinimPy* randomization algorithm counterbalancing groups by sex, age, and stroke type (ischemic/hemorrhagic) should minimize such risk, interindividual variability in lesion extent and clinical severity might be not equally distributed across the four experimental groups, precluding comparability. Third and least, the “live” on-site and at home rehabilitation activities associated to this protocol could slightly differ across patients, whereas uncontrollable factors such inner motivation or the intensity of unregulated outside activities with rehabilitative value could interfere and mask the real impact of tDCS interventions. For these reasons, on-site “live” rehabilitation programs during the treatment will be rightly monitored to make sure patients’ programs are comparable across groups and kept unchanged. Additionally, patients will be regularly questioned with regard to their daily life activities during participation in the study and all their comments will be documented.

In sum, the alarming pandemic-like rates reached by the consequences of acquired brain damage in developed societies [74] and the limitations shown by conventional monofocal TMS or tDCS approaches in post-stroke motor rehabilitation calls for the design and assessment of novel treatments in experimental double-blind, controlled trials. Our protocol will test an innovative tDCS-based strategy, easy to implement clinically, aiming at modulating associated structures contributing respectively to sustained attention and cognitive control by dorsolateral prefrontal networks and also to visuo-motor adaptation by anterior lobe cerebellar regions. More generally, beyond pure clinical applications in motor improvement after an MCA stroke, our study is designed to provide insight on the anatomical and physiological foundations of motor impairments and tDCS neuroplastic phenomena driving recovery. Finally, if our intervention demonstrates clinical efficacy, our protocol will pave the way for the development of individually customized tDCS strategies based on multi-site interventions at a larger scale and the design of more sophisticated and better-adapted neuromodulation technologies.

